# Robotic versus Open Pancreatoduodenectomy for Pancreatic and Periampullary Tumors (PORTAL): a study protocol for a multicenter phase III non-inferiority randomized controlled trial

**DOI:** 10.1186/s13063-021-05939-6

**Published:** 2021-12-27

**Keywords:** Robotic, Robot-assisted, Minimally invasive, Pancreatoduodenectomy, Whipple, Pancreatic cancer, Outcomes, Recurrence, Survival

## Abstract

**Background:**

Pancreatoduodenectomy is a complex and challenging procedure that requires meticulous tissue dissection and proficient suturing skills. Minimally invasive surgery with the utilization of robotic platforms has demonstrated advantages in perioperative patient outcomes in retrospective studies. The development of robotic pancreatoduodenectomy (RPD) in specific has progressed significantly, since first reported in 2003, and high-volume centers in pancreatic surgery are reporting large patient series with improved pain management and reduced length of stay. However, prospective studies to assess objectively the feasibility and safety of RPD compared to open pancreatoduodenectomy (OPD) are currently lacking.

**Methods/design:**

The PORTAL trial is a multicenter randomized controlled, patient-blinded, parallel-group, phase III non-inferiority trial performed in seven high-volume centers for pancreatic and robotic surgery in China (> 20 RPD and > 100 OPD annually in each participating center). The trial is designed to enroll and randomly assign 244 patients with an indication for elective pancreatoduodenectomy for malignant periampullary and pancreatic lesions, as well as premalignant and symptomatic benign periampullary and pancreatic disease. The primary outcome is time to functional recovery postoperatively, measured in days. Secondary outcomes include postoperative morbidity and mortality, as well as perioperative costs. A sub-cohort of 128 patients with pancreatic adenocarcinoma (PDAC) will also be compared to assess the percentage of patients who undergo postoperative adjuvant chemotherapy within 8 weeks, in each arm. Secondary outcomes in this cohort will include patterns of disease recurrence, recurrence-free survival, and overall survival.

**Discussion:**

The PORTAL trial is designed to assess the feasibility and safety of RPD compared to OPD, in terms of functional recovery as described previously. Additionally, this trial will explore whether RPD allows increased access to postoperative adjuvant chemotherapy, in a sub-cohort of patients with PDAC.

**Trial registration:**

ClinicalTrials.govNCT04400357. Registered on May 22, 2020

**Supplementary Information:**

The online version contains supplementary material available at 10.1186/s13063-021-05939-6.

## Background

Pancreatoduodenectomy (PD) is the surgical approach of choice for benign and malignant tumors of the pancreatic head and periampullary region, and it is considered the only potential curative treatment option [1]. It is a sophisticated operation that requires proficient surgical skills, both for the dissection of the tumor from the adjacent vascular structures and for the restoration of gastrointestinal tract continuity with the performance of the pancreatic, biliary, and gastric anastomosis. This level of surgical complexity may result in significant postoperative morbidity, and data suggest that surgeon experience [2] and hospital volume [3] are critical for the achievement of favorable outcomes in pancreatic surgery. The introduction of minimally invasive surgery (MIS) promptly led to the first report of a laparoscopic pancreatoduodenectomy (LPD) [4]; however, broader adoption of this technique was relatively slow due to multiple parameters, which include limited instrument motion range, deficient ergonomics, and a long learning curve [5]. A recent phase 2/3 randomized controlled trial comparing LPD and open pancreatoduodenectomy (OPD) was terminated early, due to increased mortality in the LPD arm [6], demonstrating further the technical limitations of the technique, as well as the importance of substantial surgeon experience in minimally invasive pancreatic surgery (MIPS).

Utilization of the daVinci® robotic surgical platform (dVSS, Intuitive Surgical, Sunnyvale, CA, USA) has demonstrated an advantage compared to laparoscopic instruments, mainly due to improved three-dimensional visualization of the surgical field, tremor reduction, and additional instrument degrees of freedom [7]. As a result, robotic pancreatic surgery has gained popularity in recent years. In robotic pancreatoduodenectomy (RPD), specifically complication rates, including postoperative pancreatic fistula (POPF), delayed gastric emptying (DGE), and bleeding [8, 9], are comparable to OPD, after surpassing the learning curve [10, 11]. Additionally, estimated intraoperative blood loss, postoperative pain, and length of stay appear to be improved in RPD [12, 13]. Yet, the significant costs of the robotic platform and the lack of robust evidence to demonstrate meaningful benefit have also raised concerns in the surgical community regarding its generalized acceptance [14].

The integration of robotic pancreatic surgery in China was initiated in high-volume centers for patients with pancreatic disease, early in the development of MIS. This process allowed for optimal identification of the learning curve, assessment, and development of training, and deeper integration of the robotic surgical approach for the management of patients with pancreatic disease [11]. Since most clinical evidence for robotic surgery is based on single-center retrospective case series and non-randomized data, the need for a randomized controlled trial to objectively assess the feasibility and patient outcomes in RPD is evident, as indicated by the recent consensus guidelines on MIPS [15]. This report describes the study design and protocol of the PORTAL trial, a non-inferiority multicenter randomized controlled trial, conducted in seven national high-volume centers for pancreatic and robotic surgery. The primary goals of this trial are to prospectively [1] assess and compare the time from surgery to functional recovery between patients who undergo OPD versus RPD and [2] investigate the percentage of patients who initiate postoperative adjuvant chemotherapy within 8 weeks from surgery in a sub-cohort of patients with pancreatic adenocarcinoma.

## Methods

### Trial design

The PORTAL trial is a multicenter randomized controlled, patient-blinded, parallel-group, phase III non-inferiority trial performed in seven high-volume centers for pancreatic and robotic surgery in China (> 20 RPD and > 100 OPD annually in each participating center). Eligible patients for enrollment will be randomized in a 1:1 ratio to one of the two trial arms: robotic pancreatoduodenectomy and open pancreatoduodenectomy.

### Patient population

All patients who present in the participating centers with an indication for elective pancreatoduodenectomy will be assessed for eligibility regarding trial participation. Clinical indications for the procedure will include malignant periampullary and pancreatic lesions (pancreatic adenocarcinoma, distal cholangiocarcinoma, duodenal and ampullary carcinoma), as well as premalignant and symptomatic benign periampullary and pancreatic disease (pancreatic neuroendocrine tumors, cystic lesions, and chronic pancreatitis). Eligible patients will be assessed and informed by participating registered members of the surgical teams involved in the trial at the outpatient clinics.

### Inclusion and exclusion criteria

The inclusion criteria for trial eligibility are [1] age ≥ 18 years [2]; clinical indication for pancreatoduodenectomy [3]; patient eligibility for both RPD and OPD [4]; patient performance status of 0 or 1 based on comorbidities, assessed using the Karnofsky score and the Nutritional Risk Screening Tool (NRS-2002) score; and [5] imaging with computed tomography (CT) and/or MRI pancreas performed within 8 weeks for benign and 4 weeks for malignant disease; for the latter, tumor staging with MRI liver, CT chest, and cancer antigen 19-9 (CA19-9) is also mandatory not earlier than 4 weeks prior to surgery.

The exclusion criteria are [1] body mass index > 35 kg/m^2^, [2] pregnancy, [3] previous history of major abdominal surgery, [4] requirement for multivisceral resection (additional surgical resection of surrounding solid organs), [5] ongoing treatment for other primary malignancy, [6] preoperative chemotherapy and/or radiotherapy in patients with pancreatic adenocarcinoma, and [7] involvement of major regional vessels by the tumor (portal and superior mesenteric vein, superior mesenteric artery, hepatic artery, celiac artery) as defined by the borderline resectable and locally advanced nomenclature [16].

### Randomization process (Fig. 1)

Eligible patients will be identified and discussed about the trial at the time of initial outpatient clinic assessment. Details will be provided to the patients about the goals and the structure of the trial and how it will affect the treatment approach. Recruited patients will be informed further in detail and will sign a written informed consent prior to treatment initiation, which can be revoked at any time. After signing the informed consent, all included patients will be randomized in a 1:1 ratio between robotic and open pancreatoduodenectomy using an online randomization module (IRT, Shanhu Health, Shanghai, China). Eligible patients will be variably randomized in equal proportions, with variable sizes blocks. After enrollment, they will be randomly stratified preoperatively based on [1] risk of developing a postoperative pancreatic fistula (POPF) using an externally validated model [17]: high risk (pancreatic duct diameter < 3 mm on preoperative CT at the pancreatic neck, and/or body mass index (BMI) > 25 kg/m^2^) versus low risk (pancreatic duct diameter ≥ 3 mm on preoperative CT at the pancreatic neck, and/or BMI ≤ 25 kg/m^2^) [2]; presence of endoscopic stenting for preoperative biliary drainage; and [3] diagnosis of pancreatic adenocarcinoma. Patient randomization and allocation between the two arms is performed with dedicated software (irtlite.irtone.com); after allocation, the patient details and allocated arm are typed into sealed envelopes by the randomization team, and the clinical nurse specialists deliver the envelopes to the appropriate surgical teams. The envelopes will be opaque and numbered with the patient trial ID number and will be opened by the responsible surgical team 1 day prior to surgery. Participating patients will be blinded to the procedure until postoperative day 5 or until functional recovery is achieved. Blinding will occur with the placement of identical wound dressings in all patients: on the presumed midline or J-incision and the placed trocars sites and extraction site incision in the RPD group and on the midline or J-incision and the presumed trocar sites and extraction site incision in the OPD group (Fig. 2a). Wound changes will occur as clinically indicated in an attempt to maintain patient blinding. This is a feasible approach that has been tested in previous randomized prospective trials [6, 18]. Unblinding of participating patients will be available as per their request; if a patient is accidentally unblinded, the event will be noted, and the patient will be excluded from the per-protocol analysis.

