The reconstruction phase starts with a single jejunal loop being passed in a retrocolic fashion through a small incision in the mesocolon on the right of the mesocolic vessels or through the tunnel under the mesenteric root. The pancreaticojejunostomy (PJ) is performed in an end-to-side fashion as a double-layer duct-to-mucosa anastomosis with interrupted 3/0 and 5/0 or 6/0 Prolene sutures for the outer and inner layer, respectively. Ten centimeters distally on the same jejunal loop, the hepaticojejunostomy (HJ) is constructed with running or interrupted 4/0 or 5/0 PDS or Prolene sutures, based on the diameter of the common hepatic duct. Lastly, the gastrojejunostomy is performed with single-layer running 3/0 V-loc (Covidien, New Haven, CT, USA) or 3/0 Vicryl sutures, or with an endostapler. If a pylorus-preserving pancreatoduodenectomy (PPPD) is decided, the subsequent duodenojejunostomy is performed in a similar fashion to the GJ. The abdomen is thoroughly inspected, and hemostasis is secured and two large-bore double-lumen surgical drains are placed in proximity to the PJ and the HJ. The specimen is extracted via the extended periumbilical trocar incision or a Pfannenstiel incision, which is closed in layers, and all trocars are removed, and skin incisions are sutured. Placement of wound catheters for postoperative pain control is optional.

Minor variations in the robotic surgical approach based on individual surgeon experience and preference, especially regarding the pancreatic and/or biliary anastomotic technique, will be discussed and accepted accordingly; documentation of any variations in patient records will be mandatory. Conversion rates from the robotic to the open procedure will be recorded in detail and assessed based on urgent and non-urgent conditions. Patients assigned in the robotic arm, who undergo a conversion procedure will be included as part of the robotic group in an intention-to-treat analysis.

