### Operative technique: open pancreatoduodenectomy

In the control arm, patients will undergo an open pancreatoduodenectomy, which is the standard of care and has a long-standing safety record. A midline or right J-shaped subcostal incision is performed for access in the abdominal cavity. The operative steps are similar to the robotic approach in terms of tumor dissection, specimen removal, and anastomotic reconstruction. Since OPD volumes in participating centers are very high with quality results, wider surgical variations from individual surgeons are anticipated. These variations will be evaluated in advance and allowed accordingly, and they will also be documented in detail in patient records.

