### Primary outcome measures

The primary outcome measure of the PORTAL trial for all participating patients is time to postoperative functional recovery, measured in days. The patients’ postoperative course will be evaluated daily by the nursing and medical staff and will be communicated to the study coordinators for documentation. Postoperative criteria that need to be fulfilled independently to achieve functional recovery status are as previously described [18]:
Discontinuation of intravenous or subcutaneous analgesia and preservation of adequate control levels (assessed by a pain score).Ability to maintain sufficient oral caloric intake as defined by the institutional dietetic services (no less than 50% of recommended dietary intake), without intravenous fluid support.Restoration of patient ambulation to an independent or preoperative level if mobility deficits were present.No clinical or biochemical signs of ongoing abdominal infection affecting the patient’s performance status: absence of fever and normalization of inflammatory markers (white cell count, procalcitonin, and/or C-reactive protein). Patients can be in oral antibiotics.

Additionally, in a sub-cohort of patients with pancreatic ductal adenocarcinoma assessed between the two study arms, the primary outcome will be the percentage of patients who achieve administration of adjuvant chemotherapy at 8 weeks postoperatively. The chemotherapy regimen will be decided by the oncology service on an individual basis and will not affect the comparison.

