Primary and secondary outcome data for both ITT and PP groups will be compared utilizing appropriate statistical methodology. Categorical variables will be represented as frequency and proportion and will be analyzed using Fisher’s exact or chi-square tests, as appropriate. Continuous variables will be presented as mean values with standard deviation (SD), or median values with interquartile range (IQR), and will be compared using the two-sample *t*-test or Mann-Whitney *U* test, as per the type of distribution. A logistic regression analysis was performed for consideration of randomization stratification, based on the predetermined parameters. Survival of patients with pancreatic adenocarcinoma between the two arms will be estimated using the Kaplan-Meier analysis method and compared between the groups with the log-rank test. The SAS software v. 9.2 (SAS Institute Inc., USA) was utilized for all statistical analyses.

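### The stated analysis of time to functional recovery ignores the seven centres and the three randomisation factors, which gives up precision on the difference in days judged against the 1-day margin

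*Protocol article*

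**What the plan says.** All references are to the protocol article.

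- *Trial design*: the trial is "performed in seven high-volume centers for pancreatic and robotic surgery in China".
- *Randomization process*: "Eligible patients will be variably randomized in equal proportions, with variable sizes blocks". The numbered list of strata begins with "they will be randomly stratified preoperatively based on [1] risk of developing a postoperative pancreatic fistula" and ends with "presence of endoscopic stenting for preoperative biliary drainage; and [3] diagnosis of pancreatic adenocarcinoma". Centre is not on it.
- *Statistical considerations and analysis*: non-inferiority is judged on a confidence interval for the difference in days, against a margin of 1 day. Continuous outcomes are compared by a two-sample t-test or Mann-Whitney test, depending on distribution. The one adjusted analysis is described thus: "A logistic regression analysis was performed for consideration of randomization stratification, based on the predetermined parameters". On the list above, those parameters do not include centre.
- *Primary outcome measures*: one of the four recovery criteria is sufficient oral intake, "as defined by the institutional dietetic services (no less than 50% of recommended dietary intake".
- *Postoperative patient care*: all centres follow a modified enhanced-recovery protocol with common milestones.

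**The concern.** Time to functional recovery is scored locally, and the intake criterion is partly local: 50% is a floor, above which each institution's dietetic service may set its own rule. Centre means may therefore differ for reasons unrelated to treatment. An unadjusted test leaves that variation in the error term. It does the same with variation explained by fistula risk, stenting and diagnosis, which were thought important enough to stratify on.

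The logistic regression does not repair this for the first primary outcome. It models a binary outcome and cannot return a difference in days with a confidence interval to set against 1 day. At stake is the width of the interval on which non-inferiority is decided, in a design with almost no power in reserve above 80%.

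**Working it through.** **Inputs from *Statistical considerations and analysis*:** SD 2.5 days, margin 1 day, power 80%, 200 per-protocol patients, 122 per arm after losses of 10%, 3% and 5%, and a decision on a 95% confidence interval. **Assumed:** the share of total variance lying between centres (ICC), 0.05 to 0.20. The article gives no value.

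**1. The plan's own figure.** n per arm = 2(z₁₋α + z₀.₈₀)² × SD² / margin².
- One-sided 2.5% (matching a two-sided 95% interval): 2 × (1.960 + 0.842)² × 6.25 / 1 = 98.1, so 99 per arm, or 100 with the t distribution. This reproduces 200. Then 100 / (1 − 0.18) = 122 per arm, or 244.
- One-sided 5%, the level stated: 78 per arm, or 156, which does not reproduce 200.

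The mismatch in significance level is a separate matter. I use one-sided 2.5% below because it matches both the sample size and the interval rule.

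**2. Effect of adjusting for centre, if 2.5 days is the total SD.** Within-centre SD = 2.5 × √(1 − ICC). SE = SD × √(2/100). Power = Φ(1/SE − 1.96).

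| ICC | Between-centre SD | Within-centre SD | SE (days) | Cut in SE | Power |
|---|---|---|---|---|---|
| 0 (or unadjusted) | 0 | 2.50 | 0.354 | – | 80.7% |
| 0.05 | 0.56 | 2.44 | 0.345 | 2.5% | 82.7% |
| 0.10 | 0.79 | 2.37 | 0.335 | 5.1% | 84.6% |
| 0.20 | 1.12 | 2.24 | 0.316 | 10.6% | 88.5% |

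**3. The price of adjusting.** Because centre was not a stratum, arm and centre are correlated by chance. With six centre terms and 200 patients the expected R² is about 6/199 = 0.03, so the SE grows by 1/√0.97, about 1.5%. The net cut is then about 1% (0.345 × 1.015 = 0.350) at ICC 0.05 and about 9% (0.316 × 1.015 = 0.321) at ICC 0.20, with power about 81.5% and 87.6%. With no centre differences at all, adjustment would cost about one point of power.

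**4. Chance imbalance is the same variance, not a further loss.** With 244 patients and ICC 0.20:
- unadjusted SE = 2 × 2.5/√244 = 0.320;
- within-centre part = 2 × 2.236/√244 = 0.286;
- between-centre part = 2 × 1.118/√244 = 0.143;
- 0.286² + 0.143² = 0.102 = 0.320².

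The unadjusted interval already contains the imbalance term. A simulation of the design (seven equal centres, eight equally likely strata, blocks of 4 or 6 assumed) agrees in size: the arm difference shifts by chance with an SD of about 0.12 day per day of between-centre SD, against 2/√244 = 0.128 from the formula.

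**5. Centre as a fourth full stratum.** 2³ × 7 = 56 cells, and 244/56 = 4.4 patients per cell. Many blocks would stay unfilled.

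**The case against.** The strongest objection is that covariates are usually left to the statistical analysis plan, which is not shown, and that this is a condensed article. That would answer a complaint about silence. But the article names its tests, and what it names is unadjusted for the days outcome. Replacing a stated method with a more precise one that uses data already collected is a fair point.

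Second, leaving centre out of the strata is a defensible choice, since 56 cells would be too many. That stands, and I do not ask for it to change. Logistic regression may also be meant for the chemotherapy outcome, which is binary and suits it. That stands too.

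Several stronger readings are tempting, and the document does not support them:

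- *That centre differences bias the comparison.* Allocation is randomised, and the unadjusted interval allows for chance imbalance (step 4). In the simulation the worst centre was typically about 13 percentage points from an even split, but an uneven split in one centre is not itself a harm.
- *That the trial is underpowered.* If 2.5 days were a within-centre SD, unadjusted power would be 78.7% to 71.6% at ICC 0.05 to 0.20. The article does not say that it is. It cites institutional data and retrospective series.
- *That each centre has its own open technique.* The text says "wider surgical variations from individual surgeons are anticipated", at surgeon level, evaluated in advance and documented. For the robotic arm it allows "Minor variations in the robotic surgical approach based on individual surgeon experience and preference". These, like the choice of robot model, belong to one arm. They are not an offset shared by both arms, and a centre term would not remove them.
- *That local discharge arrangements matter.* The endpoint is recovery, not discharge.

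The common recovery protocol and the 50% floor also limit how far centres can differ, so I do not go above an ICC of 0.20.

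**Conclusion.** The point holds as a loss of precision. As stated, the analysis of the first primary outcome uses neither the three randomisation factors nor centre, and the one adjusted analysis named cannot deliver a difference in days. If 2.5 days is the total SD and the ICC is 0.05 to 0.20, adjusting for centre cuts the standard error by about 3% to 11% before the price of about 1.5%, and raises power from about 81% to between 83% and 88%. At the low end of that range the net gain from centre is small. Any gain from the three randomisation factors would be additional, but the article gives nothing to size it with. Planned power is not reduced under the total-SD assumption, and type I error is not at risk. This is a worthwhile, inexpensive improvement and not a fatal flaw.

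**What to change.** State, before any comparison by arm, that the primary difference in days and its confidence interval come from a linear model with arm, fistula risk, biliary stenting, diagnosis of pancreatic adenocarcinoma and centre. This replaces the unadjusted test for that outcome. Keep logistic regression, with the same factors, for the chemotherapy outcome.

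Leave the randomisation scheme as it is. Leave the intake criterion as it is too: recruitment began in September 2020 (*Trial status*), and changing one component of the primary endpoint now would score earlier and later patients differently.

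The cost is a few sentences of analysis text and nine degrees of freedom (six for centre, three for the factors), plus the price of about 1.5% on the standard error shown above. No new data are needed.

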### Postoperative patient care

All participating centers are following a modified enhanced recovery after surgery (ERAS®) protocol, which focuses mainly on patient mobilization, pain management, and patient-directed oral intake and includes the following landmarks: removal of NGT on postoperative day and patient mobilization (POD) 1, clear fluids on POD 2, free fluids on POD4, and diet on POD5 as tolerated. Medical discharge will occur as a joint decision of the surgical team and the local community services that may need to be involved in the patient’s care as an outpatient. All patients are essentially declared fit for discharge as soon as functional recovery is achieved.

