### Statistical considerations and analysis

The main hypothesis in the PORTAL trial is that functional recovery of patients who undergo RPD is non-inferior to the one of patients who undergo OPD. Based on institutional historical data and information from retrospective series in the literature, the time to functional recovery in OPD is 10 days with a standard deviation of 2.5 days. Non-inferiority of functional recovery in RPD will be assessed with a non-inferiority (*δ*) margin of 10% or 1 day. With a one-sided test, a significance level of 5% (*α* = 0.05), and a power (1 − *β*) of 80%, the cohort for the trial is calculated to 200 patients (per-protocol (PP) group), using the PASS 11.0 software (NCSS, Kaysville, UT, USA) with a sample allocation ratio of 1:1 between the RPD and OPD groups. However, we anticipate a conversion rate in the RPD group of 10%, 3% incidence of occult abdominal metastatic disease in both groups, and 5% of patients to be lost to follow-up. Therefore, the final cohort will include 122 patients in each arm (intention-to-treat (ITT), Fig. 1). The main analysis will be conducted on the ITT group according to the randomized initial assignment of patients in each study arm at baseline. All enrolled patients from the ITT population who do not fulfill the aforementioned protocol violations will be included in the PP group. Additionally, patient characteristics of those who will be excluded from the PP analysis will be separately evaluated. Non-inferiority will be concluded if the lower bound of the 95% confidence interval (CI) for the difference between the two groups in time to functional recovery is not lower than − 1 day of the non-inferiority margin.

A second primary endpoint of the study is the percentage of patients with a diagnosis of pancreatic adenocarcinoma in each study arm, who will be fit for the initiation of postoperative adjuvant chemotherapy 8 weeks after the day of surgery. Institutional empirical data demonstrate that 50% and 75% of patients who undergo OPD and RPD, respectively, are eligible for adjuvant chemotherapy at 8 weeks, which is considered the optimal time for postoperative systemic treatment. With the same power and significance level as in the ITT group, 64 patients with pancreatic adenocarcinoma will be included in each arm to assess for the superiority of RPD.

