The primary endpoint of this study is functional recovery, which is a more objective evaluation of recovery and combines postoperative complications and patient-reported quality of life (QoL) outcomes. It is determined by four main parameters in the immediate postoperative period: sufficient pain control, nutritional competency, mobilization, and no evidence of ongoing inflammation [36]. Indeed, these criteria are of main interest in all patients and remain the focus of conversation during preoperative decision-making: when will the patient be able to resume his daily activities. Moreover, patient-reported outcomes are widely accepted and incorporated in patient care [37, 38]. Additionally, the concept of functional recovery is separate from inelastic variables, such as postoperative complications and/or postoperative length of hospital stay [39]; different healthcare systems around the world have different capacities for patient care management in the community [40]. However, postoperative complication rate and severity, and length of stay will be compared between RPD and OPD as secondary endpoints. The established EuroQoL Group 5-level EQ-5D questionnaire was utilized for the assessment of the quality of life [https://euroqol.org/eq-5d-instruments/]. Similar to previous randomized trials comparing minimally invasive and open surgery [41], patient blinding is being applied to reduce bias due to patient expectations and limit the effect of psychological factors associated with either of the two surgical approaches [42].

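### Patient blinding ends at postoperative day 5 or at functional recovery, without saying which governs; if the earlier event does, nearly all patients may be unblinded before the primary endpoint

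*Protocol article*

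**What the plan says.** The Randomization process section sets the blinding period: "Participating patients will be blinded to the procedure until postoperative day 5 or until functional recovery is achieved". The method is identical dressings in both arms. Dressings are changed when there is clinical need, with an effort to keep the patient blind. A patient may be unblinded on request. Accidental unblinding is noted and removes the patient from the per-protocol analysis.

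The primary outcome is time to functional recovery in days (Primary outcome measures). All four criteria must be met: pain control without intravenous or subcutaneous analgesia, judged by a pain score; oral intake of at least half the recommended amount without intravenous fluids; ambulation at an independent or preoperative level; and no sign of ongoing abdominal infection, shown by absence of fever and normal inflammatory markers. Nursing and medical staff evaluate patients daily.

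Three other places bear on the timing and purpose of blinding:

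- Statistical considerations and analysis: "the time to functional recovery in OPD is 10 days with a standard deviation of 2.5 days".
- Postoperative patient care: "free fluids on POD4, and diet on POD5 as tolerated". Table 1 first marks primary endpoint assessment at the day 8/discharge visit.
- Discussion: "patient blinding is being applied to reduce bias due to patient expectations".

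**The concern.** The two events joined by 'or' are far apart for almost every patient. Solid diet is scheduled only from day 5, and adequate oral intake is one of the recovery criteria, so few patients could meet all four by then. A center that stops blinding on day 5 complies with the sentence as written. So does a center that continues until recovery. Seven centers could apply it differently.

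This matters because three of the four criteria depend on patient report or behaviour. If patients expect an easier course after the robotic operation, those who know they had it may report less pain, eat sooner and walk sooner. That would shorten recovery in the robotic arm for reasons other than the surgery and would favour a non-inferiority conclusion. Patient blinding is the only masking the article describes, and the trial is labelled patient-blinded on this endpoint.

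The per-protocol set is affected too. If blinding lapses on day 5, it is unclear whether a patient who learns the allocation on day 6, before recovery, counts as accidentally unblinded and is excluded.

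**Working it through.** **Step 1. Confirm that the mean and SD are the real planning figures.** Inputs from Statistical considerations and analysis: SD 2.5 days, "margin of 10% or 1 day", power 80%, 1:1 allocation, true difference taken as 0.

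n per arm = 2 × (z₁₋α + z₀.₈₀)² × SD² / margin²

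- One-sided α = 0.025: 2 × (1.960 + 0.842)² × 6.25 / 1 ≈ 98.1, so 99 per arm and 198 in total. This is close to the stated 200.
- One-sided α = 0.05: 2 × (1.645 + 0.842)² × 6.25 / 1 ≈ 77.3, so 78 per arm and 156 in total. This does not give 200.

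The stated 200 fits the 0.025 level implied by a two-sided 95% interval, not the one-sided 5% in the text. That is a separate matter. Allowing for losses of 10% + 3% + 5% = 18% gives 200 / 0.82 = 243.9, so 244, as stated. The SD of 2.5 days is therefore the one behind the trial's size. The 10-day mean is consistent with the margin, since 10% of 10 days is 1 day.

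**Step 2. Share of patients recovered by day 5.** With mean 10 and SD 2.5, the standardized distance is (5 − 10) / 2.5 = −2.0. The protocol gives no distribution, so the shape is my assumption. Three shapes with the same mean and SD are shown. The 5.5-day cut allows for recording in whole days.

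| Shape | Recovered by 5.0 days | Recovered by 5.5 days |
|---|---|---|
| Normal | 2.3% | 3.6% |
| Gamma (shape 16, scale 0.625) | 0.8% | 1.8% |
| Lognormal (log-variance ln 1.0625) | 0.4% | 1.1% |

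Under the normal shape, 0.0228 × 122 ≈ 2.8, or about 3 patients per arm.

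**Step 3. What each reading implies.**

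- Earlier event governs: between 100 − 3.6 = 96.4% and 100 − 0.4 = 99.6% reach the endpoint after blinding may have ended. The average gap is about 10 − 5 = 5 days.
- Later event governs: 0% are unblinded by rule before the endpoint.

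**Step 4. Sensitivity for the robotic arm.** The 10-day mean is stated for open surgery and carries over to robotic surgery only if the means are equal. With a robotic mean of 9 days (normal, SD 2.5), 5.5% recover by day 5. With a mean of 8 days, 11.5% do. Even then, 100 − 11.5 = 88.5% reach the endpoint after day 5.

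**The case against.** The strongest reply is that the later event is the intended one. If only about 2% recover by day 5, the clause about functional recovery would almost never operate under the earlier reading. It does real work mainly if it carries blinding past day 5, and the purpose given in the Discussion fits that. This is a reasonable argument about intent, but the sentence does not say so and nothing else in the article settles it.

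A reader might infer from the step 3 percentages that the endpoint is in fact measured unblinded in nearly everyone. The document does not support that. The percentages hold under one reading only, and permission to end blinding is not disclosure: no step schedules telling the patient or removing dressings on day 5.

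A reader might also put a size on the bias, for example 0.3 to 0.5 day, which would be 30 to 50% of the one-day margin. Nothing in the document anchors such an effect, and under the later reading the unblinding rule contributes none.

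Nor is the endpoint wholly in the patient's hands. Staff rate it, intake is judged against a dietetic threshold, and the infection criterion is objective. Because the last criterion met sets the date, expectation can shorten recovery only where a patient-influenced criterion comes last. The Discussion also claims only to reduce expectation bias, not to remove it.

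Finally, accidental unblinding is already noted and leads to per-protocol exclusion. That helps, but the main analysis is by intention to treat, unblinding on request is not clearly covered, and the exclusion itself depends on when blinding is meant to end.

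**Conclusion.** The point holds in conditional form. The blinding rule has two readings with opposite consequences: about 96 to 99.6% of patients reaching the primary endpoint after blinding may have ended, or none unblinded by rule before it. The range rests on the protocol's mean and SD for open surgery, three assumed shapes and whole-day rounding. It changes little if robotic recovery is one or two days faster. Because three of the four criteria can be influenced by expectation, the outcome may be measured unblinded in most patients. Whether that happens, and how much bias would follow, cannot be determined from the document. This is more than a missing detail, since a center following the sentence as written could end blinding before the endpoint in nearly all its patients. No change in sample size follows.

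**What to change.** State that planned patient blinding continues until functional recovery is recorded, and that reaching day 5 alone does not end it. Keep the existing provisions for unblinding on request and for dressing changes when clinically needed. Record the date and reason of any unblinding before recovery, whether accidental or requested. Align the per-protocol exclusion with this rule, saying explicitly which kinds of unblinding before recovery lead to exclusion.

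Recruitment began in September 2020, so for patients already treated, report by arm when blinding ended relative to recovery.

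The cost is a wording change, a date and reason field for unblinding, and blinding dressings kept somewhat longer in most patients where centers have been stopping on day 5. The dressing method is already in place and the protocol describes it as feasible.
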